## Abstract

**Background:**

Prolonged Grief Disorder (PGD) is a psychiatric diagnosis with significant implications for individuals and society. Familiarity with its diagnostic criteria and recommended interventions is essential for early detection and effective treatment. As aging naturally involves multiple losses, older adults are at distinct risk of developing PGD, a condition associated with psychological and physical comorbidities and increased mortality. In the Israeli context, this issue holds particular significance following the events of October 7, 2023, and the ensuing war, which have had — and continue to have — a profound impact on the population’s mental health. Given PGD’s recent inclusion in diagnostic manuals, many physicians may lack sufficient knowledge, leading to under-recognition or misdiagnosis. This gap is particularly evident among older adults, for whom the assessment and management of psychological distress are often underassessed and undertreated, highlighting the urgent need for targeted training and broader integration of existing knowledge into clinical practice. Accordingly, the present study has two main objectives: (1) to assess physicians’ knowledge and use of PGD diagnostic criteria with older patients, and (2) to evaluate the effectiveness of a brief informational intervention on their understanding and diagnostic application.

**Methods:**

Using a mixed experimental design, the study will include senior physicians and residents specializing in geriatrics, psychiatry, and family medicine. Data will be collected via an online structured questionnaire containing professional background items and clinical vignettes designed to assess participants’ knowledge and application of PGD diagnostic criteria. Afterwards, participants will be individually randomized (1:1) via a computer-generated sequence in a partially participant-blinded, assessor-blinded controlled trial to either an experimental group viewing an informational PGD video or a control group viewing a structurally equivalent video (matched in length, graphics, and word count) addressing bereavement in older adults without directly referencing PGD. All participants will then complete the vignettes again to evaluate the effects of the intervention. A one-month follow-up assessment will evaluate the retention of intervention effects.

**Discussion:**

This first systematic Israeli study on PGD implementation will provide an empirical basis for policy development, professional training, and prevention programs. Its findings may enhance diagnostic accuracy, improve care efficiency, reduce systemic costs, and support ongoing evaluation and refinement of clinical practices.

**Clinical trial registration:**

## Introduction

Prolonged Grief Disorder (PGD) is a mental health condition recently included in the ICD-11 (1) and DSM-5-TR (2). It is characterized by unique core symptoms, including intense yearning for the deceased, persistent preoccupation with the deceased, or both. These symptoms are commonly accompanied by emotional pain, disruption of personal identity, loss of meaning and purpose in life, and impaired daily functioning (3). PGD is distinct from other psychiatric diagnoses such as Major Depressive Disorder, Generalized Anxiety Disorder, and Post-Traumatic Stress Disorder, and is associated with a range of negative outcomes, including physical health problems (4), increased risk of suicidal ideation or attempts, reduced life satisfaction, functional impairment, and greater utilization of health services. Epidemiological studies indicate that among bereaved populations, the prevalence of PGD is relatively low in representative samples (approximately 3–4%), while higher rates, up to 16%, are reported in non-probability or convenience samples (5).

Aging is naturally accompanied by experiences of loss and bereavement, and as individuals they encounter an increasing number of losses, including traumatic ones and various life-course separations. Consequently, older adults are considered at elevated risk for disruptions in the normative grief process in general, and for the development of PGD in particular (6, 7). Supporting evidence includes, for example, a meta-analysis of over 60,000 participants, which identified spousal loss and pre-death grief (experienced while caring for a terminally ill relative) as two major risk factors for PGD (8). Both phenomena, whose prevalence increases with age, illustrate older adults’ heightened vulnerability to the loss of significant others and its adverse consequences. Additionally, multiple studies have linked the loss of a close person, especially a spouse among older adults, to serious health outcomes, including immune dysfunction, increased cardiovascular risk, chronic pain, and even elevated mortality rates [e.g (9–11).

These findings indicate that PGD not only impacts individual quality of life but also imposes a significant economic burden on healthcare systems. Additional costs include medical treatments, medications, hospitalizations, and mental health services, alongside impaired daily functioning and productivity. Early identification and tailored intervention can therefore improve patient outcomes while reducing systemic costs [e.g (12–14).

Consistent with the gap between academic research and its systematic application in clinical practice (15), healthcare providers’ knowledge of complications in the normative grief process is often limited (16). Furthermore, given that PGD is a relatively new diagnosis not yet widely recognized among clinicians, raising awareness among physicians and mental health professionals is crucial for enabling early identification and appropriate intervention (6). This issue is especially relevant for older adults, given the evidence of underdiagnosis and undertreatment of psychological distress in this population [e.g (17, 18).

For example, although suicide rates among older adults in Israel and globally are higher than in any other age group, epidemiological studies show that the prevalence of clinically significant depression and anxiety is comparatively lower in older adults than in younger populations. Moreover, older adults with depression often report fewer typical cognitive-emotional symptoms (e.g., dysphoria, guilt, or feelings of worthlessness) and instead emphasize physical symptoms such as fatigue, somatic complaints, and difficulties with memory and concentration (19).

In fact, research indicates that many older adults who engaged in suicidal behavior had visited a physician shortly beforehand, yet their psychological distress remained undetected. This phenomenon stems, in part, from a lack of knowledge and appropriate skills among healthcare professionals regarding assessment and treatment in older populations. Additionally, research indicates the presence of ageist attitudes among clinicians, manifesting, for example, in reduced confidence in the effectiveness of interventions for the elderly. At the same time, many older adults avoid seeking mental health care for generational, social, personal, or practical reasons, making the primary care physician often the sole gateway to identifying psychological distress and referring patients for appropriate care (19). These findings highlight the need for targeted professional training to enhance understanding of the clinical characteristics unique to older adults and to facilitate effective, tailored intervention.

In the context of PGD, as noted earlier, early identification and diagnosis are crucial for prevention, improving quality of life, and reducing systemic burden and costs, as timely detection of the disorder can prevent psychological and physical deterioration and minimize unnecessary interventions. Additionally, misdiagnosis can also lead to inappropriate pharmacological treatment rather than evidence-based psychological intervention — particularly grief-focused cognitive-behavioral therapy (20), which is considered the treatment of choice for PGD (5). For example, a randomized controlled trial provided empirical evidence that PGD-focused psychotherapy effectively reduces grief symptoms, whereas citalopram (a selective serotonin reuptake inhibitor [SSRI]) did not have a significant impact on grief symptoms but did alleviate depressive symptoms in patients with comorbid depression (21). Moreover, due to PGD’s addiction-like features, recent research has focused on reward system activity in the brain, which plays a central role in the disorder (22).

In summary, PGD is a psychiatric disorder with significant implications for individuals and society. Comprehensive familiarity with its diagnostic criteria and recommended interventions is essential for early identification and optimal treatment. Aging, accompanied naturally by multiple losses, places older adults at a distinct risk for PGD, which is associated with increased mental and physical comorbidity and mortality. In Israel, this issue has gained particular significance following the events of October 7, 2023, and the subsequent war, which continue to critically affect the population’s mental health [e.g (23, 24). Since PGD was only recently included in diagnostic manuals, it is likely that many physicians are not yet sufficiently familiar with it. As a result, cases of under recognition, partial, or even incorrect diagnosis of the disorder may occur in clinical practice, leading to interventions that do not adequately address its unique characteristics. This gap is particularly pronounced among older adults, for whom the assessment and management of psychological distress are often suboptimal, underscoring the need for targeted training and broader integration of existing knowledge into clinical practice.

### Aims

The current study has two primary objectives: (1) to assess physicians’ knowledge and application of PGD diagnostic criteria in older adults — specifically geriatricians, psychiatrists, and family physicians; (2) to examine the short- and long-term impact of a brief, focused PGD intervention on physicians’ knowledge and diagnostic application.

### Expected results

The *primary outcomes* of the study are twofold. First, participants are expected to report significant knowledge gaps regarding PGD diagnostic criteria, reflecting difficulty or uncertainty in applying these criteria with older bereaved patients. Second, exposure to concise PGD-related information via a video-based intervention (with a control group viewing an equivalent video; see Methods) is expected to improve knowledge and application of diagnostic criteria. Specifically, correct responses on the clinical vignettes are expected to increase in both groups following the intervention, with a greater improvement in the experimental group compared to the control group. These improvements are expected to persist at one-month follow-up, particularly in the experimental group.

The *secondary outcome* concerns differences between medical specialties. Psychiatrists are expected to demonstrate higher baseline knowledge and application of PGD criteria compared to other participants, achieving a significantly higher proportion of correct responses on the clinical vignettes.

## Methods and analysis

### Participants

The study will employ a mixed experimental design. The target population includes senior physicians and residents in geriatrics, psychiatry, and family medicine working in diverse settings, including hospitals, clinics, geriatric centers, and private practices, who have frequent contact with older adults. Participation will be anonymous, voluntary, and based on informed consent. The sample will be recruited via convenience sampling through professional channels (e.g., mailing lists of relevant medical associations, professional social networks, and distribution via department and center administrators), aiming to ensure balanced representation across medical specialties and levels of professional training.

*Sample size:* Power analysis using G*Power (version 3.1) indicated that to detect a medium effect size (partial η² = 0.06) with 80% power and α = 0.05 in a mixed repeated-measures design with two independent variables, a minimum sample of 34 participants is required. To detect a small effect size (partial η² = 0.01) under the same conditions, 198 participants are needed. Accordingly, the study aims to recruit a sample size within this range.

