### Procedure

Ethical approval for the study was obtained from the Ruppin Academic Center Institutional Ethics Committee and the Helsinki Committee of Clalit Health Services. Participants will receive online invitations, including an explanation of the study purpose, participation procedure, and assurance of full anonymity. It will also be emphasized to participants that the questionnaire contains hypothetical scenarios intended solely to assess professional responses and does not include personal questions or require emotional disclosure. However, it will be clarified that the content may evoke uncomfortable feelings, and that participation can be discontinued at any point without any consequences. Participation will be voluntary and contingent upon providing informed consent.

In the first stage, participants will complete the online questionnaire, including background items and seven vignettes, estimated to take six minutes. The case vignettes will be presented in a randomized order for each participant to control potential order effects. Upon completing the questionnaire up to this point, participants will be asked to click the ‘Submit’ button, after which they will be prompted to indicate whether they wish to continue to the next phase of the study. This procedure is intended to ensure that the data of participants who choose not to continue are preserved and not lost. Participant responses across study stages will be linked using an identifier code, allowing for repeated-measures analyses while maintaining participant anonymity. In the second stage, participants will be individually randomized (1:1) via a computer-generated sequence in a partially participant-blinded, assessor-blinded controlled trial to either the experimental group (PGD video) or the control group (general bereavement video). In the third stage, all participants will re-answer the seven vignettes to assess the intervention’s effect on knowledge and application, taking approximately four minutes. Following completion of this stage, all participants will be asked whether they are willing to participate in a follow-up assessment. Those who consent will, at one month, receive an automated link to complete the clinical vignettes again to assess retention of the intervention effects (fourth stage). An overview of the study design is shown in **Figure 1**.

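### The sample sizes of 34 and 198 do not give the stated 80% power for partial η² of 0.06 and 0.01 as that measure is ordinarily defined; the pre-post comparison has about 29% power at each

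*Protocol article*

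**What the plan says.** The sample-size paragraph (Protocol article, Participants) reports a G*Power 3.1 calculation of the number needed "to detect a medium effect size (partial η² = 0.06) with 80% power and α = 0.05 in a mixed repeated-measures design". For this medium effect it concludes that "in a mixed repeated-measures design with two independent variables, a minimum sample of 34 participants is required". For the small effect it says "To detect a small effect size (partial η² = 0.01) under the same conditions, 198 participants are needed". Recruitment is then to fall between the two figures.

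The paragraph does not name the test, the number of occasions, the correlation between occasions or the software's effect-size option. Other sections fix most of the design. Allocation is to two arms (Procedure: "participants will be individually randomized (1:1) via a computer-generated sequence"). The vignettes are answered before and straight after the video, and again at one month by those who agree. The hypothesis under Expected results is improvement in both groups, "with a greater improvement in the experimental group compared to the control group", which is a group-by-time interaction.

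**The concern.** An effect size, a power and a sample size are stated together, so they can be checked against each other. Partial η² is SS_effect/(SS_effect + SS_error). For a group-by-time test the error term is the within-person one, so the benefit of measuring each physician twice is already inside the measure. If the calculation then multiplies by a factor for the number of occasions and their correlation, that benefit is counted twice and the required sample size comes out far too small.

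The figure of 34 is called a minimum, so the plan allows recruitment to end near it. At that size the trial would carry a claim of 80% power for a medium effect on a scale where it has under one chance in three of detecting that effect.

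**Working it through.** **Inputs.** From Participants: partial η² of 0.06 and 0.01, power 80%, α = 0.05, N = 34 and 198. From Procedure: 2 groups, 1:1. From Expected results: the group-by-time interaction. Assumed, because not stated: the number of occasions m, the correlation ρ and the effect-size scale. N counts physicians with data at every occasion analysed.

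**Step 1: convert the effect sizes.** f² = η²/(1 − η²).
- 0.06/0.94 = 0.0638, so f = 0.2526
- 0.01/0.99 = 0.0101, so f = 0.1005

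**Step 2: reproduce the plan's figures.** Take f on the single-occasion SD, for which the noncentrality is λ = f²·N·m/(1 − ρ). With m = 2 and ρ = 0.5 the multiplier is 2/0.5 = 4, so λ = 4f²N, on 1 and N − 2 degrees of freedom.
- N = 34: λ = 4 × 0.0638 × 34 = 8.68, power 81.5%
- N = 198: λ = 4 × 0.0101 × 198 = 8.00, power 80.4%

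These are the smallest even totals that reach 80%, so both published figures come out exactly. The main effect of time has the same λ and degrees of freedom here and gives the same totals. Three occasions on this scale would have given 28 and 162. Three groups by three occasions gives 36 and 201, which is close but not exact.

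**Step 3: power for partial η² as defined.** The within-person error is already in the measure, so λ is f²·N, or f²·(N − 2) on the error-degrees-of-freedom convention, with no multiplier.

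| Partial η² | N | λ | Power |
|---|---|---|---|
| 0.06 | 34 | 2.04 to 2.17 | 28.4% to 29.8% |
| 0.01 | 198 | 1.98 to 2.00 | 28.8% to 29.1% |

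A simulation of the equivalent t test on change scores (100,000 runs per case) gives 29.9% and 28.9%.

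**Step 4: N for 80% power on that definition.** About 126–128 for 0.06 and 780–782 for 0.01. At N = 198, power for partial η² = 0.06 is 94%.

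**Step 5: add the one-month visit.** With three occasions analysed and sphericity assumed, power is 41–43% at 34 and 41% at 198. The totals for 80% are then about 78–80 and 480–482.

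**Step 6: what 34 and 198 do detect.** Under the Step 2 settings the implied interaction partial η² is 4f²/(1 + 4f²).
- 0.2553/1.2553 = 0.20
- 0.0404/1.0404 = 0.039

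At ρ = 0.5 the SD of change equals the single-occasion SD, since 2(1 − ρ) = 1. A two-sample t test on change with 17 per arm has 80% power for a difference of 0.99 SD; with 99 per arm, for 0.40 SD.

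**Step 7: dependence on ρ, on the scale of Step 2.**

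| ρ | Power at N = 34 | Power at N = 198 |
|---|---|---|
| 0.3 | 68% | 66% |
| 0.5 | 82% | 80% |
| 0.7 | 96% | 95% |

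**The case against.** The strongest reply is that the calculation itself is sound. If the authors meant f of about 0.25 and 0.10 on the single-occasion SD with ρ = 0.5, then 34 and 198 are computed correctly and only the label is wrong. This stands in part. The settings are not published, so a scaling error is an inference from an exact double match, and a reader should not take it as proven that the software was misused. But the article reports partial η², not that f, and under neither reading do the printed effect sizes, power and sample sizes agree.

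A reader might also infer that the whole trial has about 29% power. The documents do not support that. The 29% belongs to the pre-post test at each sample size paired with its own effect. The target is a range, and within it the medium effect reaches about 80% at 128 and 94% at 198. Using the one-month visit raises power, though not to 80% at the stated pairs.

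Nor does the unstated correlation point only one way: on the apparent scale, ρ above 0.5 raises power as much as a lower value reduces it. The feasibility data cannot settle the matter. Only 12 physicians completed both assessments, the article gives no SD or correlation, and it offers those data in support of practicality rather than as a planning effect.

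Last, it could be said that the settings belong in a fuller document. The point here is not their absence but that three stated figures are inconsistent.

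**Conclusion.** The point holds as an inconsistency between the printed effect sizes and the printed sample sizes. For partial η² in its ordinary sense, the pre-post group-by-time test has 28–30% power at 34 and 29% at 198, against the 80% stated; with three occasions it has 41–43% and 41%. The floor of 34 does not reach the medium effect, the upper part of the planned range does, and the small effect is out of reach anywhere in the range.

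This rests on the standard definition of partial η², two equal groups, an F test at α = 0.05 and, for three occasions, sphericity. The explanation, an f on the single-occasion SD reported as partial η², is likely but inferred. The shortfall does not depend on it.

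**What to change.** Rewrite the sample-size paragraph along these lines: 34 completers give 80% power for a between-arm difference in pre-post change of about 1.0 SD (interaction partial η² about 0.20), and 198 for about 0.40 SD (partial η² about 0.04), at two-sided α = 0.05, with two occasions and an assumed pre-post correlation of 0.5.

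Remove the claims that 34 and 198 give 80% power for partial η² of 0.06 and 0.01. Add that, for the pre-post test, 0.06 needs about 128 completers, which lies inside the planned range, and 0.01 about 780. Give the power over a range of correlations, as in Step 7.

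The cost is one reworded paragraph and a less favourable stated power. Correcting the statement needs no extra participants. If 80% power for partial η² = 0.06 is to be kept as an aim on the pre-post test, the floor has to rise from 34 to about 128, still within the range.

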**Figure 1 f1:**
[figure not shown]
Study design.

Upon completion of their participation, participants in the control group will be provided access to the PGD video to ensure equitable access to professional information; this will occur immediately after the third stage for those who do not consent to follow-up, and after completion of the one-month follow-up assessment for those who do. All collected data will be stored anonymously and encrypted, with access limited to authorized researchers for study purposes only. Participants will remain anonymous throughout, and results will be reported only in aggregate form.

*Data Analysis:* To test the study hypotheses, data analysis will include descriptive and inferential statistics, including simple linear regression, one-way analysis of covariance (ANCOVA) controlling for relevant background variables (e.g., levels of professional training), and mixed-design repeated measures ANCOVA.

*Feasibility assessment:* A preliminary feasibility assessment (N = 20 physicians, of whom 16 were senior physicians) was conducted to evaluate the study procedures and materials. Baseline performance on the clinical vignettes yielded a mean correct response rate of 61.4%, broadly consistent with prior reports in the literature (e.g (27). Overall, 12 participants completed both pre- and post-intervention assessments. Preliminary patterns suggested a potential intervention effect: in the control group, correct responses increased from 59.1% pre-intervention to 65.7% post-intervention, whereas in the experimental group, correct responses increased from 63.3% to 83.7%. These observations should be interpreted with caution given the small sample size and exploratory nature of this feasibility assessment and are presented solely to support the practicality and potential utility of the study design.

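### The sample sizes of 34 and 198 are completer counts used as a recruitment range with no allowance for non-completion, so at 60% completion neither bound keeps 80% power for its own effect size

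*Protocol article*

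**What the plan says.** In the Protocol article, Participants (Sample size), a G*Power calculation is set up "to detect a medium effect size (partial η² = 0.06) with 80% power and α = 0.05", for which "a minimum sample of 34 participants is required". The next sentence reads "To detect a small effect size (partial η² = 0.01) under the same conditions, 198 participants are needed". The paragraph then sets the recruitment goal between these two numbers and mentions no allowance for people who do not complete.

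Three other places bear on how many recruits will have usable data:

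- Procedure: after the baseline vignettes, and before randomisation, "they will be prompted to indicate whether they wish to continue to the next phase of the study". The one-month stage is again opt-in.
- Feasibility assessment, on a run with 20 physicians: "Overall, 12 participants completed both pre- and post-intervention assessments".
- Expected results, among the primary outcomes: "These improvements are expected to persist at one-month follow-up, particularly in the experimental group".

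Practical and operational considerations accepts that response rates may suffer. It answers with a short questionnaire, retention of the stage-1 data, and a comparison of those who continue with those who stop. None of these changes the recruitment number.

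**The concern.** A repeated-measures power calculation counts people who have data on every occasion that enters the test. Someone who stops after stage 1 is never randomised. That person informs the first objective (baseline knowledge) but adds nothing to the comparison of the two videos. If the calculated counts become the number to recruit, the stated 80% power holds only if everybody goes on to the post-test, and the protocol's own feasibility data suggest otherwise.

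At stake is the second primary objective. A study that recruits 34 people satisfies the plan as written, but at 60% completion it would have little better than an even chance of detecting the effect it was sized for. A null result could then be read as evidence that the video does not work.

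**Working it through.** **Inputs.**
- From Participants: α = 0.05, power 80%, partial η² = 0.06 with N = 34, partial η² = 0.01 with N = 198.
- From Procedure: two groups, 1:1.
- From Feasibility assessment: 12 of 20 with both assessments.
- Not stated, therefore inferred: two occasions, correlation ρ = 0.5, sphericity, G*Power's default effect-size form. These are used because they return both stated numbers exactly.

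**Formula.** Effect size f = √(η²/(1 − η²)). For the group-by-time interaction with k = 2 groups and m = 2 occasions, the noncentrality is λ = f²·N·m/(1 − ρ) = 4f²N, with 1 and N − 2 degrees of freedom. Power is the probability that the noncentral F exceeds the central 95% point.

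**Step 1: reproduce the plan.**
- Medium: f = √(0.06/0.94) = 0.2526. N = 34 gives λ = 4 × 0.06383 × 34 = 8.68 and power 0.815; N = 32 gives 0.790.
- Small: f = √(0.01/0.99) = 0.1005. N = 198 gives λ = 4 × 0.010101 × 198 = 8.00 and power 0.804; N = 196 gives 0.7996.

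Each stated N is the smallest even number that reaches 80%. The plan's arithmetic is right, and neither figure contains a margin for loss.

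**Step 2: completion rate.** 12/20 = 0.60, exact 95% CI 0.36 to 0.81.

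**Step 3: power at 60% completion.**
- 34 × 0.6 = 20.4, about 20 completers: λ = 4 × 0.06383 × 20 = 5.11, power 0.571.
- 198 × 0.6 = 118.8, about 119 completers: λ = 4 × 0.010101 × 119 = 4.81, power 0.585.

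**Step 4: other completion rates**, each bound with its own effect size (fractional N kept, so the 60% row differs slightly from step 3).

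| Completion | 34 recruited, η² = 0.06 | 198 recruited, η² = 0.01 |
|---|---|---|
| 50% | 0.50 | 0.51 |
| 60% | 0.58 | 0.58 |
| 70% | 0.65 | 0.65 |
| 80% | 0.72 | 0.71 |
| 90% | 0.77 | 0.76 |

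With f rounded to 0.25 and 0.10, the 80% row is 0.71 in both columns.

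**Step 5: recruitment implied at 60% completion.** 34/0.6 = 56.7, so 57 (58 for equal arms). 198/0.6 = 330.

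**Step 6: one month.** No return rate is given. Assume that 60% of post-test completers return (range 50% to 80%). Then 198 recruits give 118.8 × 0.6 = 71 people (59 to 95). Under the same settings, applied to baseline versus one month, power is 0.39 at 71 for the small effect (0.33 at 59, 0.49 at 95). For the medium effect it is 0.97 at 59 and 0.99 at 71.

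**The case against.** The strongest reply is that the plan gives a range, and most of that range is safe for the medium effect. This stands. On the authors' scaling about 57 recruits restore 80% for partial η² = 0.06, and 198 recruits (119 completers) give over 99%. A reader might infer that power is below 60% whatever is recruited; the figures do not support that. The loss to under 60% applies to each bound paired with its own effect size.

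A second reply is that the completion rate comes from 20 people, in a run the protocol itself calls exploratory, and that the text does not say when or why the other eight lacked both assessments. That also stands, and the interval of 36% to 81% shows the uncertainty. It does not rescue the claim, because near the upper end of that interval power is still only about 71% to 72% at each bound.

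A third reply is that the article condenses a fuller protocol, where an allowance may sit, and that non-continuation is acknowledged. But the article itself turns the calculated counts into the recruitment goal, and the acknowledged measures leave that number unchanged.

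Three further inferences are tempting and should not be drawn:

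- That the one-month comparison is unpowered altogether. Step 6 shows that this depends on the effect size and on an assumed return rate.
- That planning for two occasions when three are measured creates a shortfall. The number of occasions is not stated, and three on the same scaling would need fewer people (28 and 162).
- That the effect-size convention in G*Power adds to the loss described here. It is a separate question from attrition, and the text does not state which option was used.

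**Conclusion.** The point holds in this form. The figures 34 and 198 are correct as numbers with both pre and post data, but the plan uses them as numbers to recruit. The stated 80% power is therefore not delivered at either bound unless completion is essentially full.

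At the feasibility rate of 60%, power is about 57% at the lower bound for partial η² = 0.06 and 58% to 59% at the upper bound for partial η² = 0.01. For the small effect no recruitment number in the range reaches 80% at that rate; for the medium effect about 57 or more does. The conclusion rests on the inferred G*Power settings, which match both stated figures, and on 12/20 as a rough guide to completion. The one-month figures rest on an assumed return rate and are only illustrative.

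**What to change.** In the Sample size paragraph, take one of two routes:

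1. State that 34 and 198 are completed stage-3 assessments (participants with both pre and post data), and give the recruitment each implies at 60% completion: about 57 and 330.
2. Keep the recruitment range of 34 to 198, and restate power for the roughly 20 to 119 expected completers, separately for the medium and the small effect.

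Under either route, give the source of the completion rate and its interval. For the opt-in one-month stage, give the expected number and the precision under a stated return-rate assumption, and do not claim 80% power for the small effect there.

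The change is wording only. Its cost is a less favourable stated power; recruiting more people is optional.
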